### Study setting

The hospital cohort study will take place within well-established acute stroke services with clinical access to CT or MR angiography (CTA/MRA) and at least daytime presence of a specialist stroke team. The ambulance cohort study will be hosted by regional ambulance services feeding into these stroke services. The research environment will reflect the local care pathway for patients with acute stroke symptoms including the scene of the incident, ambulance, emergency department and stroke service.

### Study participants

Both pre-hospital and hospital patients will fulfil the following criteria to undergo an assay reading:

Inclusion criteria:
Aged 18 years and overAt least responsive to strong stimuli during assessment of conscious level (alert, voice or pain on the Alert, Voice, Pain, Unresponsive (AVPU) scale)Face Arm Speech Test (FAST) positive or any observed new focal neurological symptoms indicating suspected acute strokePersistence of the new stroke-like symptoms during the initial clinical assessmentBelieved to be within 6 h of onset of the new stroke-like symptoms at the time of the first clinical assessmentSMARTChip assay WBPC reading can be undertaken before receipt of any reperfusion therapiesPre-hospital patients will only be included if they are to be transported to a study hospitalPatients will only be included in the hospital cohort if they have *not* had a pre-hospital reading attempted

Exclusion criteria:
Hypoglycaemia (capillary glucose <3.5mmol/l)External signs of significant acute trauma which are likely to need additional treatment (large haematomas, open wounds, limb deformity)Chemotherapy or radiotherapy treatment for cancer within the last 7 days

In order to provide a population to fulfil the objectives of the substudy, trained hospital staff (when available) will attempt an assay reading on the following subgroup of patients:
Had an assay reading attempted by ambulance personnelThe symptoms resulting in admission are believed to have commenced within 6 h of the time that the hospital assay can be performedThe hospital assay can be performed before IVT or MT if this treatment is indicated

### Participant identification and consent

Ambulance and hospital personnel will determine suitability for the SMARTChip WBPC assay from their routinely conducted clinical assessments. Because the assessment of suspected stroke patients needs to be performed rapidly in order to minimise delays in accessing time-dependent treatments, patients will be approached about study enrolment after the initial emergency assessment and treatment processes, including the SMARTChip assay(s), have been completed. A formal research consent process performed in the ambulance or immediately on hospital arrival would cause unacceptable delays.

All patients who had either an ambulance and/or hospital WBPC reading attempted will be approached for study enrolment. An assay reading attempt will be defined as a fingerprick sample procedure being undertaken. As described below (see ‘SMARTChip Purine assay (index test)’), there may be occasions when the assay technology fails to calibrate and progression to fingerprick sampling is not possible. In such cases, patients will not have undergone any research procedures, and approach for consent will not occur. However, as failed calibration provides important test usability information, non-identifiable data about the test attempt will be recorded and reported.

Approach of patients for study enrolment will be by appropriately research-trained clinical staff or NHS research support staff. Ideally, approach of patients will take place during their inpatient stay and as soon as possible after the emergency assessments and treatments have taken place such that a timely discussion about the study can be held. However, for a small number of patients, this may not be possible because of early discharge, transfer or death, and in these situations, alterative consent methods will be used as described below.

#### Consent

The consent process will seek permission for retention and analysis of WBPC assay data and collection of selected routinely recorded healthcare data which are essential to complete the study objectives. There are no additional study-specific assessments.

### Consent for patients who can be approached about study participation during their inpatient stay

#### Consent for patients with mental capacity

For patients with capacity to consent to research, a trained member of the clinical team or NHS research support staff will approach the patient to discuss the study and provide a patient information sheet. After allowing sufficient time for potential participants to decide whether to take part in the study and an opportunity to ask questions, consent will be obtained in writing. When a patient has mental capacity but is unable to sign the consent form (e.g. because of weakness of the dominant hand following stroke), consent will be confirmed orally in the presence of a witness (an individual not otherwise involved in the trial), and the witness will sign and date the consent form on behalf of the participant.

If a potential participant is due to be discharged and wishes to have longer to consider the information before making a decision, staff will provide a postal consent form and prepaid reply envelope which can be returned if a decision to take part is made.

#### Consent for patients with mild communication difficulties

For patients with mild communication difficulties due to the effects of a stroke or mimic condition, a set of ‘easy access’ study documentation will be used. After allowing sufficient time for the information to be considered and an opportunity to ask questions, consent will be obtained in writing using the ‘easy access’ consent form.

If a potential participant is due to be discharged and wishes to have longer to consider the information before making a decision, an ‘easy access’ postal consent form and prepaid envelope are available for use. Staff will consider the appropriateness of such forms prior to issue including the availability of a relative/friend to assist with completion. If a postal form is judged to be inappropriate, the potential participant will be offered the opportunity to return for further discussion and consent at a later date.

#### Consent for patients who lack mental capacity

It is anticipated that approximately one third of study eligible patients will be unable to engage with an informed consent process due to the effects of stroke and mimic conditions upon communication and cognition. As exclusion of this group would drastically reduce the clinical relevance of the study, if a patient is unable to provide consent, a personal or nominated (professional) consultee will be approached as further described below.

It is anticipated that the majority of patients will be approached about participation within 24 h of admission which is typical for clinical trials of emergency stroke care. If at this time, a potential participant is believed to be lacking in capacity to consent to research, the staff making this first approach (appropriately trained clinical staff or NHS research support staff) will confer with the attending clinical team to determine the likelihood that this patient will improve and recover capacity by 48 h after admission. If it is considered that the patient is unlikely to recover capacity in this time, staff will proceed to attempt to identify an appropriate personal consultee (usually the next of kin) to approach, discuss the study and provide a consultee information sheet. If a personal consultee is identified, after allowing sufficient time for him/her to consider the patient’s wishes and feelings and an opportunity to ask questions, the consultee will be asked to complete a consultee declaration form if they believe that the patient would have no objection to taking part in the study. If the potential participant is due to be discharged and the personal consultee wishes to have longer to consider participation, staff will provide a postal personal consultee declaration form and prepaid reply envelope which can be returned if a decision to take part is made.

In the event of being unable to locate an appropriate personal consultee by 48 h after admission, an independent clinician (nominated consultee) will be approached to confirm that the patient lacks capacity for consent and that study participation would not introduce a risk of harm or be against the patient’s wishes from what is known about their character and beliefs. The independent clinician will sign a nominated consultee declaration form concerning study participation.

If when a patient is first approached they are believed to be lacking in capacity to consent to research and after conferring with the clinical team it is considered that the patient is improving and therefore may recover capacity to discuss the study, approach about consent will be delayed for 24 h. A further review of capacity will then be undertaken. If at this time the patient has recovered capacity, staff will proceed to seek consent directly from the patient. However, if the patient remains unwell and lacking in capacity, staff will proceed as described above to approach a personal consultee or independent clinician.

#### Consent and early mortality

The early mortality rate following acute stroke is approximately 10%. Some mimic conditions are also associated with a high mortality, e.g. severe infection. Exclusion of patients that die soon after admission would reduce the study’s relevance for the typical suspected stroke population.

If a patient who underwent a SMARTChip assay attempt dies before consent can be obtained using one of the approaches described above, the local principal investigator will sign an Early Mortality Declaration Form to confirm that the patient has died, and take responsibility for the use of routinely collected healthcare data for this research project.

##### Consent for patients who are only identified after discharge or transfer from the admitting hospital

Patients who are only identified as having undergone a SMARTChip assay after discharge or transfer from the admitting hospital will be invited to take part by post. An invitation letter, participant information sheet, consent form and prepaid return envelope will be mailed. The letter will include a telephone number of the admitting hospital research team to answer any queries or discuss the study in more detail. Patients willing to take part in the study will be asked to return a completed consent form.

As it will not be possible to assess mental capacity or communication issues prior to a postal invitation, the invitation letter includes a specific section for a person reading the letter who is not the intended recipient but reading it on their behalf. The reader is informed that the recipient can take part in the research and is asked to contact the hospital team for discussion and further information. If contacted, the hospital team will discuss the study and offer either a face-to-face appointment to obtain consent or to post the appropriate form (i.e. the easy access postal consent form or the personal consultee postal declaration form).

For invited patients who have not returned a consent form within 2 weeks, or where there has been no other contact about an invited patient, the local hospital research team will follow up with one telephone call.

##### Changes in capacity to consent to research during participation in the study

As there are no additional study-specific assessments and only collection of routinely available healthcare data in this project after the SMARTChip assay, changes in capacity status will not be reviewed.

##### Consent not obtained

If a patient or a consultee declines the invitation to be included in the study or a postal consent form is not returned, or if consent by one of the approaches above is not obtained for any other reason, collected data will be retained at the local site to document that a SMARTChip assay measurement(s) was undertaken but no further study data will be collected. The researchers will be informed that a test was conducted but consent was not obtained and no further data will be provided.

Figure 2 summarises the decision process for obtaining study consent.

**Fig. 2 Fig2:**
[figure not shown]
Decision process for study consent

### SMARTChip purine assay (index test)

The diagnostic technology under evaluation comprises four tiny electrochemical biosensors printed in carbon on strip of ceramic substrate (50 × 10 × 1 mm) (called ‘SMARTChip Purine’) and a bespoke portable reader device. A coupled cascade of three enzymes (adenosine deaminase, purine nucleoside phosphorylase and xanthine oxidase) detects the combined concentrations of the purines: adenosine, inosine and hypoxanthine. To take a measurement, the user inserts the SMARTChip into the reader, performs a calibration and buffer step and then adds a drop of blood from a fingerprick sample. The procedure takes 6 to 8 min and can be completed in parallel with other aspects of the standard emergency care pathway for suspected stroke. As the study is blinded, the assay reading is not displayed anywhere and is only accessible to the researchers in the data downloaded from the reader (see below).

There may be occasions when an assay step fails, i.e. calibration, buffer or the WBPC measurement. If any step fails, to repeat the assay, a new SMARTChip is required. In the pre-hospital setting, only one attempt using one SMARTChip will be permitted to avoid the possibility of causing delays to patient transport to hospital, e.g. if calibration fails, the procedure will be abandoned at this point. For the hospital setting, if the calibration or buffer step fails, up to two further attempts will be permitted as this is unlikely to delay care (i.e. use up to three SMARTChips). However, only one fingerprick will be permitted and therefore only one attempt at the blood measurement step.

Following any assay attempt, the bespoke reader device will be connected to a designated password-protected study laptop, and reading data will be downloaded. Data will subsequently be provided to the research team (consented patients only) either manually via encrypted USB drives or over the internet. No patient identifiable data is added to the reader or downloaded into the study laptop.

#### Verification of WBPC assay results

Each WBPC assay result combines readings from the four individual SMARTChip electrodes. Due to the conditions under which SMARTChip will be deployed during the study, including handling by users who are less familiar with the technology, it is possible that the electrical contacts, electrodes or enzyme coating are damaged. Even though the SMARTChip passes the calibration stage, one or more of the four small electrodes may produce readings which are not physiologically or electrochemically plausible. The raw data from an assay passes through additional reader software to compute the WBPC result. This software will label the readings as electrochemically plausible ('verified') or not. All data will be used in the study analyses, but 'verified' and ‘unverified’ results will be handled separately (see ‘Main ambulance and hospital study analyses’ section).

In addition, staff from Sarissa Biomedical (technology manufacturer) will subject the biosensor current readings to an automated check using validated software. This is to review that the data quality controls within the reader are functioning appropriately. In the event that the automated check suggests a malfunction (for example a verified reading should be unverified or vice versa), a report will be prepared and presented to the study steering committee who will make a decision about whether there is justification to alter the reading accordingly. The automated check will occur without access to any clinical data, and any alterations will be recorded.

Unverified readings may be related to malfunctioning SMARTChips or user error, and this will be monitored by staff from Sarissa Biomedical. If there is a clustering of unverified readings associated with a particular production run of SMARTChips; then, others from that batch will be replaced and local storage conditions reviewed. If the assay data generated by any user shows a pattern suggestive of incorrect SMARTChip use, the user will be invited to attend refresher training.

### Reference standards (comparator)

#### Main study

For the main study, reference standards are required to assign the following clinical diagnoses which constitute the suspected stroke population: ischaemic stroke, haemorrhagic stroke, TIA and stroke mimic conditions. Whilst brain imaging tests are available which objectively confirm haemorrhagic stroke, no single diagnostic test exists for ischaemic stroke, TIA and many stroke mimic conditions. Because of this, diagnoses will be assigned by a local hospital expert clinician and confirmed via independent adjudication as described in detail below.

Hospital expert clinician opinion informed by brain imaging ± other investigations as clinically appropriate will be used to select a diagnosis from a predefined diagnosis framework (Table 1). This framework is being used because primary medical diagnoses recorded in medical records can vary according to the taxonomy used and the terminology preferred by individual clinicians, e.g. chest infection is synonymous with pneumonia, bronchopneumonia and lower respiratory tract infection. Clinicians will be asked to select a ‘definite’ or ‘probable’ primary clinical diagnosis according to the framework. As diagnoses are sometimes uncertain for a time after admission to hospital, clinicians will be asked to provide the diagnosis assigned at 7 days after hospital admission or at discharge/death if sooner. The framework includes an option for ‘unclear’ if the clinician cannot assign a diagnosis. In order to facilitate consistent completion of the framework, guidance has been developed to assist clinicians in allocation of a definite, probable or unclear diagnosis (Table 2).

**Table 1 Tab1:**
[figure not shown]

[figure not shown]

[figure not shown]
Primary diagnosis framework

**Table 2 Tab2:** Guidance for completion of the primary diagnosis framework

Framework diagnosis	Clinical information may include	Investigations	Secondary prevention planned
**Definite stroke/TIA**	Symptoms typical for a vascular territory. Time course typical of stroke or TIA. Vascular risk factors are present.	Imaging supports the clinical diagnosis with no suggestion of an alternative aetiology.	Full (as appropriate)
**Probable stroke/TIA**	Symptoms mostly typical of a vascular territory. Time course suggestive of stroke or TIA. No vascular risk factors or a less common cause of stroke or TIA.	Imaging supports the clinical diagnosis with no suggestion of an alternative aetiology. No mimic diagnosis suggested by other investigations	Full (as appropriate)
**Definite mimic**	Positive clinical evidence from history/examination and/or previous medical history consistent with a mimic condition	Evidence consistent with a mimic diagnosis on CT/MRI imaging or other investigations.	No new secondary prevention.
**Probable mimic**	Symptoms more suggestive of a mimic than a vascular territory. Vascular risk factors may be present. No relevant PMH of a mimic condition	No CT or MRI evidence of new stroke but no alternative imaging diagnosis. No mimic diagnosis suggested by other investigations.	No new secondary prevention.
**Unclear**	Symptoms not typical of a vascular territory and/or time course not typical of stroke or TIA. No reason for stroke or TIA to occur. No positive clinical evidence from history/examination or previous medical history consistent with a mimic condition	No CT or MRI evidence of new stroke but no alternative imaging diagnosis. No mimic diagnosis suggested by other investigations.	Simple or no new secondary prevention considered appropriate.

Following assignment of a diagnosis, clinical and imaging data collected for the study will be reviewed by an independent clinician at the study coordinating centre to determine if the diagnosis assigned and clinical/imaging information concur. If data do concur, the assigned diagnosis will be confirmed as appropriate. If the data do not concur, the case will be discussed by a Diagnostic Adjudication Committee which will comprise a stroke specialist from the study coordinating centre team, the local hospital clinician responsible for assigning the diagnosis and another local clinician who was not involved in making the diagnosis. All are blinded to the SMARTChip assay outcome. The committee will meet by teleconference and review anonymised routine clinical information available up to day 7 or discharge if sooner, to agree a diagnosis.

In addition, irrespective of whether the local diagnosis assigned and clinical/imaging data concur or not, where ‘unclear’ or ‘probable’ stroke mimic diagnoses (categories B–J in the framework) are selected, Diagnostic Adjudication Committee review will take place. This is to check that there is reasonable evidence that these categories are appropriate as typically there will be greater reliance upon clinical judgement than objective information from any routine investigations.

For ‘unclear’ cases, if the committee cannot reach consensus (e.g. because of missing clinical information or lack of adjudicator consensus), the final diagnosis will still be listed as ‘unclear’, and these patients will not be included in the diagnostic accuracy analyses as it has not been possible to determine any diagnosis. Data for these participants will still be reported. All other diagnoses will be used in the analyses as described in the ‘Statistical analyses’ section.

#### Substudy

For the substudy, a reference standard is required for ischaemic stroke with LVO. Angiography of the cerebral circulation via CT or MR imaging conducted as part of standard clinical care will be used. Angiography is not routinely performed for all suspected stroke patients as clinical or non-contrast radiological examination can decree it unneeded. It is usually performed for patients with National Institute for Health Stroke Scale (NIHSS) [20] score of >5 presenting within 6 h of symptoms onset, where plain CT has not shown a haemorrhage or another radiological diagnosis for the acute symptoms, e.g. tumour.

For patients undergoing CT or MR angiography (CTA or MRA), LVO will be defined as present if angiography demonstrates reduced filling in any large branch of the anterior cerebral circulation as assessed using the Ten Point Clot Burden Score [21]. A score <10 will indicate the presence of LVO. All CTAs will be reported by a consultant neuroradiologist blinded to patient and study information. Local clinical routine imaging reports will also be obtained if available, but these will not alter the data to be used for the main study analyses. The frequency and nature of any discrepancies between the reports will however be reported on study completion.

For participants who do not undergo angiography because they do not meet the clinical criteria (e.g. mimic conditions, haemorrhagic stroke, mild ischaemic stroke with NIHSS < 6 and TIA) and the probability of LVO is remote, it will be assumed that they do not have LVO. However, there may also be participants with ischaemic stroke of sufficient severity to be potentially caused by LVO (i.e. NIHSS >5), but who do not undergo angiography. This is usually because of an early clinical judgement that they would not be offered MT (e.g. due a low Alberta Stroke Program Early CT Score [22] or significant comorbidities) or because MT is not available. For these participants, it will not be possible to make a confident assumption about LVO status, and therefore, their data will not be included in diagnostic accuracy analyses concerning LVO. Available data for these participants will still be reported.

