**Fig. 1 Fig1:**
[figure not shown]
SMARTChip technology

The SMARTChip assay could be used to triage patients with suspected stroke symptoms into those people likely to have a non-stroke mimic condition and those likely to have true stroke. The assay may have maximum impact if deployed pre-hospital but may also be of use on arrival at hospital for patients who do not present to the ambulance service, or if the technology is not available in the ambulance or was not deployed by ambulance practitioners because stroke was not suspected. In both settings, the assay result would be useful for determining whether patients with suspected stroke symptoms continue along the stroke emergency assessment pathway or whether they should be directed to other more appropriate emergency services for further assessment and treatment (i.e. the test result indicates that a patient is likely to have a non-stroke mimic condition).

The SMARTChip assay may also have an alternative purpose in the context of suspected stroke. Due to the greater volume of brain tissue involved during LVO stroke, it is hypothesised that WBPC readings will be elevated higher and for a longer time period when compared to both mimic conditions and those stroke patients without LVO. Sequential SMARTChip assay readings may therefore be able to assist in identification of patients with LVO stroke. As time-critical mechanical thrombectomy treatment is only available in a small number of regional neuroscience centres (comprehensive stroke centres), patients with LVO suitable for thrombectomy typically require secondary transfer from a HASU. Rapid identification of mechanical thrombectomy-eligible patients could facilitate transfer and expedite access to treatment.

The main aim of this study is to evaluate the diagnostic accuracy of the SMARTChip assay for identification of stroke mimic conditions amongst the suspected stroke population when used in either the pre-hospital or hospital environment. An exploratory substudy will be conducted to assess whether serial WBPC values could be useful for the identification of LVO stroke.

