#### Substudy

To explore the diagnostic accuracy of two sequential SMARTChip assay WBPC readings for identification of LVO stroke using a reading obtained in the pre-hospital setting and a second reading obtained in the hospital settingTo develop and retrospectively explore the diagnostic accuracy of a statistical model which combines routinely available clinical data with pre-hospital- and hospital-obtained SMARTChip WBPC readings to predict the presence of LVO

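### The LVO substudy targets LVO stroke in any territory, but its reference rule recognises only anterior-circulation occlusion, so a posterior occlusion seen on angiography would be analysed as LVO-absent

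*Protocol article*

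**What the plan says.** All references are to the protocol article.

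- **Objectives.** Under Study objectives, Substudy, the first aim is "To explore the diagnostic accuracy of two sequential SMARTChip assay WBPC readings for identification of LVO stroke" and the second is to use clinical data with "SMARTChip WBPC readings to predict the presence of LVO". The substudy items under Statistical analyses repeat both aims. None of these places names a territory.
- **Target of the reference standard.** Reference standards, Substudy opens with: "For the substudy, a reference standard is required for ischaemic stroke with LVO". Again no territory is named.
- **Operational rule.** The same section then says, for patients who have CT or MR angiography: "LVO will be defined as present if angiography demonstrates reduced filling in any large branch of the anterior cerebral circulation", assessed with the Ten Point Clot Burden Score. The cut-off is: "A score <10 will indicate the presence of LVO".
- **Handling of other patients.** Patients without angiography in whom LVO is judged remote are taken as not having it. Patients with ischaemic stroke and NIHSS above 5 but no angiography are left out of the LVO accuracy analyses. Local imaging reports are collected but do not change the analysis data.
- **Rationale.** The Background gives a biological hypothesis, "Due to the greater volume of brain tissue involved during LVO stroke, it is hypothesised that WBPC readings will be elevated higher", and a possible use: "Rapid identification of mechanical thrombectomy-eligible patients could facilitate transfer and expedite access to treatment".

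**The concern.** The condition named in the objectives is wider than the condition the reference standard can detect. A patient with, for example, a basilar occlusion visible on CT angiography and normal filling of the anterior branches has a large vessel occlusion in the ordinary sense of the objectives, yet does not meet the rule for LVO. Unless something else intervenes, that patient joins the comparator group.

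Two things are at stake. First, if the assay reads high in such a patient, a correct detection of the named target is counted as a false positive. That works against specificity, which the substudy threshold is chosen to maximise. Second, the results would describe accuracy for anterior-circulation LVO under the unrestricted label LVO. Because the misclassification comes from a rule and not from chance, recruiting more patients does not reduce it.

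**Working it through.** **Step 1: does the text let such a patient into the LVO-absent group?**

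- *Entry.* Study participants admits FAST-positive patients or those with any new focal neurological symptom suggesting acute stroke. The ambulance data fields list visual loss and double vision among the symptoms. Nothing excludes posterior presentations.
- *Classification.* With angiography, LVO is present if an anterior branch shows reduced filling (score below 10). Normal anterior filling does not meet that rule.
- *Exclusion.* The only exclusion based on LVO status is ischaemic stroke with NIHSS above 5 and no angiography. A patient who had angiography is not covered by it.
- *Correction.* Local reports cannot change the analysis data. The blinded-read checklist (Imaging data) has the clot burden score and a general entry for other pathological findings, but no named item for posterior vessel occlusion.
- *Analysis.* The substudy uses logistic regression with LVO as a binary outcome.

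Read together, these place the patient among the LVO-absent. The article does not say so in words; it follows from the rule, the cut-off and the lack of any exclusion.

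**Step 2: how large is the effect?**

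The article states no substudy sample size, LVO rate or posterior share, so there is no figure to reproduce. Every input below is an assumption.

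*Illustration A.* 300 analysable patients; 30 with anterior LVO; 270 true negatives; true specificity 80%, so 0.20 × 270 = 54 false positives; posterior occlusions *n* = 1.5, 3.0 or 4.5 (5%, 10% or 15% as many again as the 30); 80% of LVOs flagged, whether anterior or posterior.

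Apparent specificity = 1 − (54 + 0.8*n*) / (270 + *n*)

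| *n* | Calculation | Apparent specificity |
|---|---|---|
| 1.5 | 1 − 55.2/271.5 | 79.7% |
| 3.0 | 1 − 56.4/273 | 79.3% |
| 4.5 | 1 − 57.6/274.5 | 79.0% |

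For positive predictive value, 0.8 × 30 = 24 anterior LVOs are flagged.

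- At *n* = 1.5: against all LVO, (24 + 1.2)/79.2 = 31.8%; as the rule would report it, 24/79.2 = 30.3%.
- At *n* = 4.5: against all LVO, (24 + 3.6)/81.6 = 33.8%; as reported, 24/81.6 = 29.4%.

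*Dependence on the flag rate.* If posterior occlusions are flagged at the 20% background rate, then at *n* = 3.0 specificity is 1 − (54 + 0.6)/273 = 80.0%, which is no change. Below that rate it would rise.

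*Illustration B, wider ranges.* Let *p* be the share of patients with LVO in any territory, *q* the posterior share of those, and sensitivity 70%.

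Apparent specificity = [spec(1 − *p*) + (1 − sens)*pq*] / [(1 − *p*) + *pq*]; apparent PPV = true PPV × (1 − *q*)

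| *p* | *q* | True specificity 80% becomes | True specificity 90% becomes |
|---|---|---|---|
| 5% | 5% | 79.9% | 89.8% |
| 10% | 10% | 79.5% | 89.3% |
| 20% | 20% | 77.6% | 87.1% |

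At *p* = 10%, *q* = 10% and specificity 90%, PPV falls from 43.8% to 39.4%.

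**Step 3: compare with sampling error.** With 270 negatives and specificity 80%, the 95% half-width is 1.96 × √(0.8 × 0.2/270) = 4.8 points. The largest shift in illustration A, about 1 point, is roughly one fifth of that.

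**The case against.** The strongest reply is that the article states its operational definition openly. LVO in the analysis section is then a defined term, and an anterior-only target may be a deliberate choice. The article condenses a fuller protocol, and the source for the clot burden score is not at hand, so the handling of an unusual imaging finding may be written elsewhere. Posterior cases could also be found after the event from the free-text imaging results, the clinical stroke subtype, the discrepancy report and the permitted post hoc analyses.

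Part of this stands. The definition is disclosed, the substudy is exploratory with no stated minimum accuracy, and no conclusion about LVO has yet been drawn. What does not stand is that disclosure settles the matter: the section that gives the anterior-only rule opens by naming an unrestricted target, and nowhere is the substudy described as anterior-only. The ability to identify these patients later does not take them out of the negatives. The plan also already leaves out patients whose LVO status is merely uncertain, so keeping a demonstrated posterior occlusion as a negative sits badly with its own principle.

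A reader might infer three stronger claims that the document does not support:

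- *That thrombectomy eligibility is an objective the rule fails.* It is Background rationale; the substudy objectives name only LVO.
- *That specificity is certainly biased downwards.* This requires posterior occlusions to be flagged more often than other negatives. The hypothesis about tissue volume makes that plausible, but nothing in the article says that posterior occlusions involve comparable volume.
- *That the study's accuracy results are seriously distorted.* The illustrated shift is small, and the mimic analyses do not use the LVO classification.

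**Conclusion.** The mismatch between target and rule is real and minor. The stated target covers LVO in any territory, while the rule recognises anterior-circulation LVO only. As written, a posterior large-vessel occlusion seen on angiography with normal anterior filling would be analysed as LVO-absent.

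If such patients have raised readings, specificity and PPV for LVO are understated. In illustration A the specificity loss is about 1 point or less; it reaches 2.4 to 2.9 points only where 20% of patients have LVO and 20% of those occlusions are posterior. PPV falls in proportion to the posterior share. These sizes rest on assumed prevalence, posterior share, accuracy and flag rate. The more lasting consequence is the label: accuracy for anterior-circulation LVO would be reported as accuracy for LVO. The main hospital and ambulance analyses, and the targets of 377 and 935, are unaffected.

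**What to change.** Reconcile the target and the rule:

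1. State the target as anterior-circulation LVO in the substudy objectives, the opening of the substudy reference standard, the substudy analyses and the wording planned for conclusions.
2. Add one item to the existing blinded neuroradiology checklist to record posterior large-vessel occlusion on the CT or MR angiograms already being reviewed.
3. Keep patients with that finding, and no anterior occlusion, out of the LVO-negative group in the primary substudy analysis, and report their number and readings separately.
4. Add a sensitivity analysis that counts them as LVO, so that readers can see accuracy for the wider condition.

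This needs no new imaging and no further patient contact. The cost is some rewording, one checklist item and a few patients leaving the primary substudy analysis. It is cheapest to do before the images are read. It reaches only patients who have angiography; those without it stay under the existing assumption and exclusion rules.
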